### PD_Pal Intervention

The proposed PD_Pal intervention is the result of a systematic approach, where we first explored the views of healthcare professionals and patients on palliative care in the Netherlands (25, 36, 37). Subsequently, these findings were translated into the intervention: trained nurses and a workbook for patients. The specifically trained nurses, labelled as PD_Pal nurses in this study (see below), will be coordinating transmural, integrated, and proactive palliative care, including ACP, through regular conversations with patients and their FC. The conversations are supported with a patient-directed “Parkinson Support Plan—workbook,” designed to be used at home by the patient and FC to document their wishes and preferences related to end-of-life care, to prepare and guide the conversations with the PD_Pal nurse. The plan is structured within four steps (Table 1). These steps are based on previous theories [e.g., ACP (16)], shared-decision making (38), The Chronic Care Model (39), and empirical studies [e.g., interventions guiding ACP conversations that describe healthcare models or interventions aimed to provide care aligned with patients' needs, values, and preferences on all domains of palliative care, for example, physical, social, psychological, spiritual, and financial (40–43)]. The initial workbook was reviewed by a panel of five Dutch patients and caregivers and subsequently adapted based on their feedback. To make the workbook suitable for the international study, the PD_Pal nurse training started with a critical review of the workbook, and adapted to the national situation, where needed. Given the comprehensive scope of the workbook, the intervention goes beyond the clinical management of PD consequences.

**Table 1 T1:** Defined steps in the Parkinson support plan.

**Step**	**Aim**
1—Individual care plan	Describe current health and caregivers, and identification of current needs related to care and care coordination.
2—Proactive care plan	Identify expected future challenges and care needs per domain (e.g., physical, social, psychological, spiritual, and financial). The leading theme in this step is: “What is needed for good care, now and in the future?” There is also attention for challenges and needs, as experienced by the family caregiver.
3—Quality of life and end-of-life plan	Identify and document the patient's ideas about quality of life, and preferences related to end-of-life care (e.g., surrogate decision maker; life prolonging procedures; and hospital or nursing home admissions).
4—Coordination and revision plan	Discuss and plan how the “Parkinson Support Plan” will be coordinated and reviewed in the future (e.g., contact (newly assigned if not already assigned) care coordinator, update him/her about the plan, and facilitate him/her in consulting a Parkinson expert when necessary; decide when and how the “Parkinson Support Plan” will be reviewed). The PD_Pal nurse and the dyad will allocate the referred to the assigned care coordinator, to guarantee continuity of the integrated palliative care beyond the PD_Pal study.

#### The PD_Pal Nurse

The PD_Pal nurses are trained to assist the participating patients in taking the four steps of the Parkinson Support Plan. The training consists of (1) face-to-face sessions to develop skills necessary to assist the patient during the intervention, including skills to deal with emotions, and (2) monthly digital coaching sessions with the intervention-coordinator ([name]) where experiences can be discussed. Nurses will be selected based on the following criteria:

Previous experience in nursing (preferably on a “Bachelor of Nursing” or comparable level);Experienced in delivering care for people with Parkinson's disease and/or atypical parkinsonism syndromes OR experienced in delivering palliative care;Being able to visit patients at home/at a clinical centre;Able to speak and write in English (training will be held in English);Being able or willing to talk about the end of life; andOpen attitude toward (differences in) patients' preferences and values in life.

The delivery of the intervention (e.g., setting, timing, frequency, and content) will be tailored as much as possible to the patient's and FC's preferences and possibilities. Although the duration of the total intervention is tailored to patients' preferences, the study design and timeline mandate the following limits: the first conversation with the PD_Pal nurse should be scheduled up to 4 weeks after randomisation and the last conversation up to 6 months after the randomisation.

#### The Control Group

Patients in the control arm receive care-as-usual from their neurology and/or home care team. The care-as-usual and the extent to which ACP is part of this care are expected to differ among the participating countries.

### Recruitment and Consent

Several methods to reach the target group are employed, building upon the experiences with patient recruitment in the Care for Late Stage Parkinsonism (CLaSP) study (5, 44). First of all, the participating neurology clinics recruit participants from their outpatient and inpatient clinics and registries of patients who have indicated to be interested in research participation. Neurology clinics can only act as a recruitment centre if they do not offer palliative care services themselves. Second, the study centres will contact geriatricians, general practitioners, nursing homes, patient advocate groups, and self-help groups to draw attention to the project and identify and recruit eligible patients. Identified clinicians give written information to patients about the study, and if patients are interested and willing, the clinician completes a standard referral form and sends it to the local research team. The research team will contact the patient by phone, explain the trial, check the eligibility criteria as far as possible in a phone call, and will send the full information package. Patients will have at least 1 week to consider participation. If a patient provides verbal consent to contact their FC, the research team will approach the FC and invite the FC for participation as well, following the same procedure as outlined for the patient.

Patients who are interested in participation, meet the selection criteria, and have provided their initial, verbal consent will be given a first appointment for a screening visit with a study assessor, which could be a physician (neurologist, geriatrician, or psychiatrist), study nurse, or trained researcher. During the screening visit, information about the study will be explained again, and if the participant still agrees, the informed consent form will be signed. Subsequently, eligibility criteria will be verified in the screening visit, before collecting any baseline clinical and demographic data. In case the eligibility criteria can be verified based on a telephone interview and review of the medical records, written informed consent will be obtained without a screening visit. All participants will be able to withdraw their informed consent to parts or to the overall participation at any point in time.

### Randomisation, Blinding, and Treatment Allocation

Participants are considered to be enrolled into the study following written informed consent, confirmation of eligibility, and allocation of the participant ID number. After inclusion, a patient will participate in the baseline assessment (t0), after which the patient will be randomized to either the intervention or the control group (1:1) by a computer-generated algorithm embedded within the certified eCRF system. A member of the research team will communicate to the patient and FC the group to which they have been assigned.

The trial is single-blinded, as patients and their FCs cannot be blinded for treatment allocation. Participants are urged not to discuss their allocation status with the blinded study assessor, who is responsible for the data collection. At each visit, the assessor will record to which study arm they think the participant was allocated, which will allow us to assess the efficacy of the blinding.

### Study Endpoints

#### Primary Endpoint

The primary endpoint is defined as the percentage of participants with documented ACP decisions in at least one of the patients' medical records assessed at 6 months (t1) after baseline. We believe it is important to choose an outcome measure that is as close as possible to the intervention. The choice of documentation of ACP decisions as the primary endpoint was prompted by a number of considerations. One of these is that even though discussing ACP is a crucial part of the intervention, such a discussion by itself does not ensure better care, and adequate documentation is therefore a further prerequisite. Another consideration is that this endpoint proved to be sensitive to change in similar interventions targeting other populations (40).

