### Sample Size Calculation

We assume that 5% of the target population will have documented ACP wishes at baseline. The study is powered to show a 20% absolute increase from a baseline of 5% (control group) in the primary outcome measure, that is, documented ACP-decisions, at 6 months, with a power of 0.80, a statistical significance of 0.05 (two sided) and an intraclass correlation coefficient (correcting for clustering within countries) of 0.10, by a Fisher's exact test. With the above assumptions, 74 patients in each treatment group are required. The sample size will be increased to 93 patients in each treatment group for allowing a 25% dropout rate within the 6-month follow-up period for the primary outcome effectiveness evaluation.

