### Assessment Scheme

The baseline assessment (t0) consists of an in-person interview performed by the study assessor. The baseline assessment takes place either in the outpatient clinic setting, at the patient's home, or remotely via a video connection. In addition, the patient and FC complete a set of questionnaires that are self-administered. Within 2 weeks after the baseline assessment, a participant is randomized to either the intervention or the control group. For all participants, two follow-up assessments are thereafter foreseen (t1 and t2). After completion of the t2 assessment, the patient and FC will be invited for an optional semi-structured interview about end-of-life issues. Table 2 presents all assessments and the instruments that will be used to evaluate the (cost-)effectiveness and feasibility of the PD_Pal intervention.

**Table 2 T2:** Overview of the assessment schedule and its instruments, to evaluate the (cost-) effectiveness and feasibility of the PD_Pal intervention.

**Scales/domains**	**Instruments**	**Application at**		
		**T0**	**T1**	**T2**

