**Quantitative motor symptom assessment**				
Motor symptom assessment^***^	PDMonitor	X	X	X

*
*in case the patient dies during follow-up;*

**
*intervention group only;*

*** *Optional element of the study protocol; T0, Baseline after inclusion; T1, 6 months after randomisation (intervention completed); T2, 12 months after randomisation (long-term follow-up)*.

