### Statistical Analysis

#### Primary Endpoint

To evaluate the effectiveness of the intervention, all analyses of endpoints will be done in the intent-to-treat population. The primary efficacy analysis will be to investigate the effect of the PD_Pal intervention on the percentage of patients with documented ACP decisions from baseline to month 6 in the intervention and care-as-usual group. This will be tested by means of the Mantel Haenszel estimate method and by using multilevel logistic regression model, with data clustered within countries and with categorical factors (groups) and baseline characteristics as covariates, in order to test which independent variables (indicators) contribute to the effect of the intervention. The primary analysis will be repeated for the t2 assessment (12 months after randomisation) and also using the per-protocol population to confirm the overall study results. All tests will be performed two-sided, and *P*-values < 0.05 will be considered statistically significant.

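### The primary endpoint is timed from baseline in one place and from randomisation in another, and the plan leaves unclear how ACP decisions already documented at t0 enter the test

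*Protocol article*

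**What the plan says.** **Definition.** The Study Endpoints section states: "The primary endpoint is defined as the percentage of participants with documented ACP decisions in at least one of the" charts held on the patient. Its time point is given as "assessed at 6 months (t1) after baseline". This is a status at t1, and the abstract uses the same time origin. Nothing limits it to decisions made after randomisation.

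**Analysis.** Statistical Analysis, Primary Endpoint, describes the effect on the "percentage of patients with documented ACP decisions from baseline to month 6". The same paragraph times the repeat analysis at t2 from randomisation.

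**Schedule.** The Table 2 footnote gives "T1, 6 months after randomisation (intervention completed") and lists T0 separately as the baseline after inclusion. Assessment Scheme: "Within 2 weeks after the baseline assessment, a participant is randomized" to one of the two groups. The PD_Pal Nurse section allows "the last conversation up to 6 months after the randomisation".

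**Prior documentation.** Sample Size Calculation: "We assume that 5% of the target population will have documented ACP wishes at baseline". The same 5% then serves as the control rate at 6 months, against 25% with the intervention. The exclusion criteria in Study Population cover patients already receiving palliative or hospice care, but not patients with an existing ACP record. Table 2 schedules the ACP chart review at T0, T1 and T2.

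**The concern.** Two things are unsettled for the one endpoint that decides the trial.

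The first is the time origin. If the chart is closed 6 months after baseline, a patient randomised 2 weeks after baseline may still have a permitted conversation ahead. That conflicts with the footnote's statement that the intervention is complete at T1. Documentation produced by late conversations would be missed. The loss falls mainly on the intervention arm, although late documentation in controls would be missed too.

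The second is what is counted. Under the definition, a patient with an ACP record at t0 is a success in either arm whatever the intervention does. The analysis wording can be read as status at t1, as the change between two chart reviews, or as decisions newly recorded in the window. These readings classify such patients differently. The Control Group section expects ACP in usual care to differ among countries, so the number of such patients may differ by country as well.

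**Working it through.** **1. Reference figures.** Planning rates are 5% v 25%. The evaluable number is 93 × 0.75 = 69.75, about 70 per arm. Exact two-sided Fisher power, ignoring clustering, is 0.908 at 70 per arm and 0.924 at the stated 74. The stated 74 is not itself reproduced from the stated inputs: exact Fisher without clustering needs 55 per arm for 80% power. That is a separate matter, and nothing below depends on it. All power figures here ignore the stated ICC of 0.10, so they compare readings of the endpoint and do not forecast the trial's power.

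**2. Time origin.**

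| Place | t1 or t2 counted from |
|---|---|
| Abstract; Study Endpoints | baseline |
| Table 2 footnote (T1, T2) | randomisation |
| Statistical Analysis (t2) | randomisation |
| Study Design | end of the intervention phase, the intervention being given in the first 6 months after randomisation |

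Let g be the gap from baseline to randomisation, 0 to 2 weeks. A baseline-anchored t1 falls 26 − g weeks after randomisation. Assume that new documentation in the intervention arm is uniform over weeks 4 to 26 (22 weeks) and that controls stay at 5%. The share missed is g/22.

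- g = 1: 1/22 = 4.5%; 20 × 0.045 = 0.9 points; 25% becomes 24.1%; Fisher power at 70 per arm 0.885.
- g = 2: 2/22 = 9.1%; 20 × 0.091 = 1.8 points; 25% becomes 23.2%; power 0.858.

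The second line applies the maximum gap to every patient. Week 4 is the latest date for the first conversation, so documentation may start earlier. Uniform over weeks 0 to 26, the loss at g = 2 is 2/26 = 7.7%, giving 23.5%. Documentation bunched near the end would lose more.

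**3. Status against new documentation.** Let b be the share with ACP at t0, and c and t the shares of the remainder who newly document in the control and intervention arms. Assume that a record present at t0 is still there at t1.

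- Status at t1: b + (1−b)c v b + (1−b)t; difference (1−b)(t−c).
- New documentation among all patients: (1−b)c v (1−b)t; difference (1−b)(t−c).

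The risk difference is the same; only the variance differs. The plan's rates imply c = 0 and t = 0.20/0.95 = 0.2105.

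| b | Status | New | Difference (points) | Fisher power, status | Fisher power, new |
|---|---|---|---|---|---|
| 5% (plan) | 5% v 25% | 0% v 20% | 20 and 20 | 0.908 | 0.997 |
| 15% (assumed) | 15% v 32.9% | 0% v 17.9% | 17.9 and 17.9 | 0.638 | 0.991 |

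The variance term p₀(1−p₀) + p₁(1−p₁) in the first row is 0.0475 + 0.1875 = 0.235 for status and 0 + 0.16 = 0.16 for new documentation. On the planning rates, all control successes (5 of 5 points) and a fifth of intervention successes (5 of 25) would pre-date randomisation.

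**4. What stratifying for t0 status recovers.** In the Mantel–Haenszel test each stratum contributes x₁ − m₁s/N, with variance m₁m₀s(N−s)/[N²(N−1)], where s is the number of successes. In the stratum with ACP at t0 everyone is a success, so s = N and the variance is zero. That stratum drops out, and a test of status stratified by t0 ACP rests on new documentation alone.

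Check by simulation (40,000 trials, 70 per arm, no clustering, continuity-corrected test), with b = 5%, c = 3% (assumed) and t = 21.05%. Status is then 0.05 + 0.95 × 0.03 = 7.85% v 25%. Power is 0.73 unstratified and 0.88 stratified. With b = 15% and the same c and t (17.6% v 32.9%), it is 0.48 and 0.83.

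**The case against.** The case for leaving the text alone is reasonable. Most of the document already counts from randomisation, the gap is at most 2 weeks, and the average loss is about one percentage point. The analysis wording can be read as the change between the t0 and t1 chart reviews, which fits a sample size framed as an increase from baseline; no sentence says that only new decisions count. Prior documentation is built into the planning rates, and on those rates power is 0.908 before clustering. Centres with a palliative care model and patients in palliative care are excluded, so baseline ACP may well be low. Baseline characteristics enter the model as covariates, and their list commonly belongs to the analysis plan, which is not shown.

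All of this limits the size of the point. It does not remove the conflict over t1, which stands in the text: the footnote treats baseline and randomisation as separate events, so the two origins are not synonyms. The change reading is a third candidate and does not settle which quantity is tested.

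A reader might also infer more than the documents support:

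- **That prior ACP biases or dilutes the comparison.** It does not. Randomisation balances it and the risk difference is identical under both counts; the cost is efficiency.
- **That an early cut-off harms the intervention arm only.** Controls who document late are missed as well.
- **That power is about 0.64.** That figure needs an assumed 15% baseline prevalence and an unadjusted Fisher test, which is not the stated primary analysis.
- **That the endpoint must become newly recorded or revised decisions.** That is a debatable change of estimand, and it could credit trivial edits.

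**Conclusion.** The point holds at moderate importance. The time origin of t1 is contradictory, and a baseline-anchored t1 can precede the end of the permitted intervention by up to 2 weeks. The effect is small: from 25% to about 24% at a 1-week gap and about 23% at the maximum, assuming uniform documentation over weeks 4 to 26.

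Separately, the definition counts decisions made before randomisation and the analysis wording does not say which quantity is tested. This causes no bias in the risk difference. It adds variance that the t0 chart review could remove. On the plan's 5% baseline, with an assumed 3% new documentation among controls without ACP, stratifying raises power from 0.73 to 0.88 at 70 per arm without clustering. The gain is larger if baseline ACP is commoner than planned. The 3% and 15% figures are assumptions, and the calculation takes a t0 record to persist to t1.

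**What to change.** 1. Count t1 and t2 from randomisation in the abstract, the endpoint definition, Table 2 and the analysis section, with the same chart cut-off rule in both arms.
2. Make the analysis section match the endpoint definition: the percentage with a documented decision at t1, compared between arms.
3. Name ACP documentation at t0 as a stratification factor in the Mantel–Haenszel analysis or as a covariate in the logistic model. If nearly all patients with ACP at t0 are successes at t1, that covariate predicts the outcome almost perfectly and its coefficient may not be estimable. Stratification avoids this problem.
4. Report new documentation since randomisation, among patients without ACP at t0, as a supportive analysis.

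The t0 chart review is already scheduled, so no visit or instrument is added. The cost is wording and slightly more analysis work. The status endpoint and its estimand stay as they are.

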#### Secondary Endpoints

Secondary endpoints relate to the expectation that patients and their FCs will experience a better quality of life, improved care coordination, and a reduced patient symptom burden and that FC will experience an improved quality of life, in a cost-effective manner.

#### Other Endpoints

To characterize the population, we will collect demographic and social information from the participants. Furthermore, we will evaluate the feasibility aspects of the intervention and we will document what is needed to tailor the intervention procedures and materials to country-specific characteristics (e.g., differences in language and organisation of care).

In those participants enrolled in the trial who provide a separate consent, wearable sensor data will be collected, by using the PDMonitor system. The PDMonitor system consists of five devices which will be attached to both shanks and wrists and the lower back. Each device contains an accelerometer, a gyroscope, and a magnetometer. The PDMonitor is a CE-marked product, certified as Medical Device class IIa. The system has been validated for PD-related motor-symptoms, for example, bradykinesia, dyskinesia, tremor, freezing of gait, gait disturbances, postural instability, ON/OFF conditions, and response fluctuations (45, 46). In PD_Pal, data will be recorded during daily living after baseline (t0), and after each follow-up visit (t1 and t2), for five consecutive days (morning to evening) for a maximum of 12 h per day. The data will be used for further validation and exploratory analysis, for example to see if the data can serve as a predictor for the primary and secondary outcomes (e.g., how activity level and severity motor symptoms measured at home are related to the frequency of ACP arrangements, or patients' and caregivers' quality of life).

### Assessment Scheme

The baseline assessment (t0) consists of an in-person interview performed by the study assessor. The baseline assessment takes place either in the outpatient clinic setting, at the patient's home, or remotely via a video connection. In addition, the patient and FC complete a set of questionnaires that are self-administered. Within 2 weeks after the baseline assessment, a participant is randomized to either the intervention or the control group. For all participants, two follow-up assessments are thereafter foreseen (t1 and t2). After completion of the t2 assessment, the patient and FC will be invited for an optional semi-structured interview about end-of-life issues. Table 2 presents all assessments and the instruments that will be used to evaluate the (cost-)effectiveness and feasibility of the PD_Pal intervention.

**Table 2 T2:** Overview of the assessment schedule and its instruments, to evaluate the (cost-) effectiveness and feasibility of the PD_Pal intervention.

**Scales/domains**	**Instruments**	**Application at**		
		**T0**	**T1**	**T2**
